#### Missing data.

There will be missing values related to dropout and nonresponse to surveys at different time points. If there is excessive or differential attrition across BFNP, BF no-chronic pain, and Healthy Control groups, we will identify baseline characteristics that differ between participants who did and did not have missing values. We will apply sensitivity analysis, such as inverse probability weighting methods, as needed [47]. If the procedure yields different results for the hypothesis tests, we will report study outcomes both with and without sensitivity analysis. Also, it is possible that participants may be found ineligible after study enrollment. Any data collected from these participants will not be included in the data analysis.

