## Methods

### Study design and setting

This study will utilize a prospective cohort study design (Fig 2). We will enroll participants who have sustained rotational ankle (specifically AO/OTA 44 types A-C [15]) fractures that are treated operatively. Fracture patients will complete clinic assessment sessions at standard of care visits, including their first post-op appointment (2–4 weeks), at 5–9 weeks, at 3–5 months post-operatively, and at a 6–9 months follow-up visit. Clinic assessment sessions will include completion of questionnaires, blood draw, thermal imaging, quantitative sensory testing, and clinical assessment of infection, fracture healing, and radiographic arthritis. Questionnaires will be completed over the phone or in-person at each approximate time point. These visits will allow assessments during the subacute and chronic stages of BFNP. If fracture participants do not show for the in-person standard of care 6-month visit, the participant will be contacted by phone to collect patient reported outcomes (PROs). Along with this, at 1–1.5 years out the patient may be called for self-reported outcomes to assess if patients reporting chronic pain at 6–9 months still have persistent pain. A separate group of 40 uninjured healthy control participants will perform the same assessments during one study session. Enrollment procedures, including assessment of inclusion/exclusion criteria and informed consent, will occur in study session 1. This study was approved by the Indiana University (IU) Institutional Review Board. The study began January 1^st^, 2024 and will be completed on December 31^st^, 2028. We currently have 6 clinical subjects to date and expect to complete enrollment in June 2028. Data collection and results will be completed in 2029. No analysis has been implemented at this time.

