**Fig 2 pone.0327605.g002:**
[figure not shown]
Prospective cohort study design.

**Study design.** This study is an observational cohort study of patients with rotational ankle fractures. Patients will be followed longitudinally, with assignment of patients into 3 groups at >6 months after surgery for fracture repair. The distinction between the *Pain* and *No Pain* cohort will be based on the Chronic Pain Grading Scale (CPGS), with a CPGS of 0 at >6 months defining *No Pain* and a CPGS ≥1 defining the *Pain* Cohort. Several pain states may exist in the *Pain* Cohort. The Douleur Neuropathique 4 (DN4) will be used to identify patients with *BFNP* as described in the text. Patients not meeting *BFNP* will be placed in the *Other Pain-state* group (e.g., CRPS, inflammatory pain, arthritis, pain from complications). This group will be further divided into patients with CRPS and those without based on the CRPS Research Criteria. This study will focus on identifying early biomarker signatures that can discriminate between *No Pain* and *BFNP*. Biomarkers include quantitative sensory testing (QST), mRNA expressions and immune cell activation, and thermography.

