### Participants

#### Sample size.

For fracture patients, we will enroll 265 participants who have sustained rotational ankle (specifically AO/OTA 44 types A-C [15]) fractures that are treated operatively. For control patients, we aim to enroll up to 40 healthy adults, who have never sustained a bone fracture. We will attempt to enroll the same percentage of males and females as the fracture patients.

The sample size was calculated based on the limited data from literature and our experiences on prior studies [16–18]. Dietz et al. reported that patients with fracture or trauma that developed complex regional pain syndrome (CRPS) had higher scores for pain, disability and all patient-reported outcomes than fracture controls [18]. Specifically, the effect sizes of the differences between these two groups were calculated as: Cohen’s d = .31 for neuropathic pain symptom inventory (NPSI), d = .34 for current pain, and odds ratio = 7.4 of developing allodynia. Hall et al. reported the percentage of Brief Pain Inventory (BPI – today’s pain) as 55%, 58% and 34% in the 1st, 2nd and 6th months, respectively, among 53 limb fracture patients [19]. In addition, Rbia et al. [7] and Friesgaard et al. [19] reported that about one in four ankle fracture patients would develop persistent neuropathic pain. Data on other outcomes are sparse. Based on the above information and assuming type one error of α = 0.05 and correlation between repeated measures as ρ = 0.6 and ratio for group size as 1:4, we estimated the total sample size needed to achieve sufficient power (β ≥ 0.8) were n = 205 for NPSI, n = 170 for current pain and for allodynia, and n = 213 for BPI. To maximize our ability to detect the differences, we chose the largest sample size n = 213. Our experiences following fracture patients longitudinally revealed 17% attrition rate (internal surveillance data for PREP-IT studies) [17,20]. We conservatively assumed the overall attrition rate to be 20%. Therefore, a total sample of N = 265 (expected to generate 53 BFNP patients) would need to be recruited.

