### Outcome measurements

#### Measurement of BFNP in fracture patients.

The Chronic Pain Grading Scale (CPGS) will be used to determine whether fracture patients have chronic pain in the chronic phase of injury (3–5 month visit and 6–9 month visit). Fracture patients who report persistent pain (non-zero score on the CPGS) at 3–5 months and 6–9 months will also complete the Douleur Neuropathique 4 (DN4) questionnaire at the 3–5 months and 6–9 month visits.

**Chronic Pain Grading Scale (CPGS).** The CPGS grades chronic pain as a function of pain intensity and pain-related disability reported by the participant for the last three months [22]. The subscale score characteristic pain intensity will be used to categorize participants into those with and without chronic pain [23]. This item is the sum of three questions (current pain, worst pain, average pain over last month), each scored on an 11-point Likert scale with responses ranging from 0–10 for a maximum of 30 points. The participant will be asked to report only on pain related to the site of fracture. Participants scoring 1–30 on the characteristic pain intensity score in the last month at the site of fracture will be classified as having chronic pain. Patients reporting no pain (0) at the site of fracture in the last month will be classified as having no chronic pain. This tool has been used to assess chronic pain following trauma [23–25]. Internal consistency is acceptable with Cronbach’s alpha ranging from 0.67 to 0.74 depending on chronic pain condition and Kappa coefficient from 0.79 to 0.86. The CPGS has also shown good concurrent and prognostic validity [22,26].

**Douleur neuropathique 4 (DN4).** The DN4 is a validated and reliable screening tool for neuropathic pain consisting of 7 items [27,28]. The items relate to pain quality (i.e., sensory and pain descriptors) and are based on interview with the patient. The items of the DN4 are scored based on a yes (1 point)/no (0 points) answer. This leads to a score range of 0–7. The cut-off value for the classification of neuropathic pain is a total score of >3 [28,29]. The DN4 has been used to identify neuropathic pain in ankle and wrist facture patients [7,19].

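### The attrition check compares groups that exist only after the 6–9-month outcome is known, so it cannot detect differential loss of that outcome

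*Protocol article*

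**What the plan says.** Four parts of the Protocol article bear on this point.

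- **Missing data.** The rule reads: "If there is excessive or differential attrition across BFNP, BF no-chronic pain, and Healthy Control groups, we will identify baseline characteristics" that differ between those with and without missing values. A separate sentence adds: "We will apply sensitivity analysis, such as inverse probability weighting methods, as needed". Results with and without the sensitivity analysis are promised only if the hypothesis tests come out differently.
- **Study design (Fig 2 legend).** The fracture cohort is followed "with assignment of patients into 3 groups at >6 months after surgery for fracture repair". The no-pain group is fixed "with a CPGS of 0 at >6 months defining" it, and the DN4 then separates BFNP from other pain states.
- **Control subjects study visit.** Controls have a single session.
- **Sample size.** "We conservatively assumed the overall attrition rate to be 20" per cent, giving 265 fracture patients with 53 expected to have BFNP.

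Two further statements limit the problem. Under Measurement of BFNP in fracture patients, those with non-zero CPGS "will also complete the Douleur Neuropathique 4 (DN4) questionnaire at the 3–5 months and 6–9 month visits". Under Study design and setting, if the 6-month in-person visit is missed, "the participant will be contacted by phone to collect patient reported outcomes (PROs").

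**The concern.** A check for differential attrition needs a grouping that is known for everyone at risk of dropping out. Here two of the three groups are defined by the outcome that dropout removes, and the third has no follow-up to drop out from. For loss of the outcome label, the comparison therefore contains no information.

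Patients with much residual pain, or with none, may plausibly differ in their willingness to return. If so, patients with a label are a selected part of the cohort. The BFNP versus no-chronic-pain contrasts in pain modulation and immune markers, and the prediction models trained on labelled patients, would carry that selection. The group-wise comparison would not show it.

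Other parts of the plan do not close the gap. The call at 1–1.5 years is described as following up patients who reported chronic pain at 6–9 months (Study design and setting) or who were determined to have BFNP (Table 3 footnote), so it is not aimed at supplying missing labels. The stratified 70/30 split and the 100 repeats of the machine-learning workflow reuse the same labelled patients.

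**Working it through.** **1. The plan's own figure.** Inputs from Sample size: 213 evaluable, 20% attrition, 265 enrolled, 53 BFNP expected.

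- Inflation: 213 / (1 − 0.20) = 266.25, rounded up to 267. The stated 265 is within 1% of this.
- Completers: 265 × 0.80 = 212. Lost: 265 × 0.20 = 53.
- BFNP: 53 = 212 × 0.25 (one in four of completers), which is also 265 × 0.20 (the 1:4 group ratio applied to everyone enrolled).

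**2. What the group comparison can show about loss of the label.**

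| Group | How membership is known | Loss to the 6–9-month label |
|---|---|---|
| BFNP | CPGS and DN4 at more than 6 months | 0%, because membership requires the label |
| BF no-chronic pain | CPGS at more than 6 months | 0%, for the same reason |
| Healthy control | Enrolment | None possible, one visit |
| Fracture patients lost earlier | No final group | Not in the comparison |

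**3. What this can hide.** Let x be the number of the 53 unlabelled patients who would have had BFNP, with 53 BFNP and 159 others among the 212 completers. The others are the no-pain and other-pain-state patients together.

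- BFNP rate in all 265 = (53 + x) / 265. With x = 0 it is 53/265 = 20%. With x = 53 it is 106/265 = 40%.
- True attrition in BFNP = x / (53 + x). With x = 0 it is 0%. With x = 53 it is 53/106 = 50%.
- True attrition in the others = (53 − x) / (159 + 53 − x). With x = 0 it is 53/212 = 25%. With x = 53 it is 0%.

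The table in step 2 is the same for every x from 0 to 53.

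**4. Sensitivity to the inputs.**

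- With the 1:4 share, about 42 of 212 completers have BFNP (212 × 0.20 = 42.4). True BFNP attrition then runs from 0% to 53/95 = 56%, and attrition in the others from 53/223 = 24% to 0%.
- With the 17% attrition the team has observed, 265 × 0.17 ≈ 45 are lost and 220 remain, of whom 220 × 0.25 = 55 have BFNP. The rate in all 265 then lies between 55/265 = 21% and 100/265 = 38%.

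Both calculations treat every lost patient as unlabelled. Each label recovered by telephone narrows the range.

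**The case against.** The strongest case on the other side is that the section is looser, and less harmful, than it first looks. Most of this stands as a limit on the point.

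- **The comparison is not empty for all missing data.** A reader might infer that the differential check can never be evaluated, or always passes. The documents do not support that. The section covers dropout and survey nonresponse at different time points. A patient labelled by telephone has no thermography, blood, sensory testing or immune analysis at 6–9 months (Table 3 footnote), and a labelled patient may have missed an earlier visit. Those gaps can be compared between the fracture groups.
- **Weighting is not blocked.** A reader might infer that weighting depends on finding differential attrition. The if-clause leads only to a comparison of baseline characteristics. Weighting is one example of a sensitivity analysis, to be used as needed, and excessive attrition is an alternative trigger that requires no label. A threshold for it may well stand in an analysis plan that is not shown, so its absence is not counted here.
- **An unweighted completers analysis is not stated as the default.** No section says how incomplete records enter the growth models, and Data analysis already explores missingness for each measure before testing.
- **Earlier status exists.** Patients lost after the 3–5-month visit have a CPGS from it, and a DN4 if the CPGS was non-zero. This gives a provisional status, but it is not the group that the attrition rule names.
- **The 20% to 40% range is an extreme bound.** It concerns BFNP incidence, which is not a primary aim, and does not measure bias in the biomarker contrasts.

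None of this makes the three-group comparison able to show differential loss of the label. The article states a specific rule, and that rule conflicts with its own group definition. This is more than detail left to another document.

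**Conclusion.** The point holds in a limited form. As written, the attrition comparison cannot detect differential loss of the 6–9-month outcome label, because patients lost before it have no group and controls have no follow-up. It can detect only missing measures among labelled patients.

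The potential size is up to 53 of 265 fracture patients, equal in number to the whole expected BFNP group, with a worst-case BFNP rate of 20% to 40% against 25% in completers. This rests on the planned 20% attrition, on one in four completers having BFNP, and on no label being recovered by telephone. It is a bound and not a forecast. The documents give no basis for a figure on bias in the biomarker contrasts or the prediction models.

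The change should be made. The present text does not make the planned analyses invalid.

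**What to change.** Redefine the attrition check in the Missing data section:

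1. Assess attrition within the enrolled fracture cohort only, and leave controls out.
2. Compare patients with and without a 6–9-month label on first-visit data: patient and injury characteristics, PROMIS scores, Pain Catastrophizing Scale and thermography. Where available, add 5–9-week data and 3–5-month CPGS/DN4 status. Table 3 starts sensory testing at 5–9 weeks, so it cannot serve as a first-visit variable.
3. Do this regardless of group-wise attrition.
4. As a prespecified sensitivity analysis, weight the main BFNP versus no-chronic-pain contrasts by the inverse probability of having a label. Report them next to the unweighted results whether or not the two differ.

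The existing group-wise comparison can stay for missing sensory-test, blood and earlier-visit data among labelled fracture patients.

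The cost is modest extra analysis and somewhat wider intervals for the weighted results. Weighting inside the repeated nested cross-validation would be more work and can be optional. Weighting corrects only for selection explained by the measured variables, and the report should say so. All the variables are already collected. The article states that no analysis has been done, and 25 of 64 enrolled fracture patients had completed the 6–9-month visit by 31 May 2025, so the change can still be made in advance.

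### The plan promises results with and without the attrition sensitivity analysis only for the case where the hypothesis tests differ, so a material change in an estimate need not be shown

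*Protocol article*

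**What the plan says.** The Missing data section of the protocol article sets out three conditional steps.

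- An attrition check begins on this condition: "If there is excessive or differential attrition across BFNP, BF no-chronic pain, and Healthy Control groups". Neither term is quantified.
- Then: "We will apply sensitivity analysis, such as inverse probability weighting methods, as needed".
- The reporting rule follows: "If the procedure yields different results for the hypothesis tests, we will report study outcomes both with and without sensitivity analysis".

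The trigger for showing both analyses is thus the outcome of the tests. The section sets no criterion on the size of the estimate, its direction or its interval. No other section says what is shown when the tests agree.

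The Sample size section supplies the scale. On loss to follow-up it says "We conservatively assumed the overall attrition rate to be 20" (per cent). It plans on standardised effects of 0.31 for the neuropathic pain symptom inventory (NPSI) and "d = .34 for current pain".

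**The concern.** A sensitivity analysis for attrition is meant to show how far the answer moves when the missing-data assumption changes. Whether p crosses 0.05 in both analyses is a poor measure of that. With some 43 patients in the smaller group, both the non-significant range and the significant range are wide enough for two materially different estimates to fall on the same side.

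Reporting then depends partly on the results. A reader who sees one estimate cannot tell whether weighting left it alone, doubled it or halved it. This matters because missing biomarker data are expected. Besides the assumed 20% attrition, the procedures calendar (Table 3) carries out sensory testing, blood draw and thermography at 6–9 months only when the visit is in person.

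**Working it through.** **Inputs from the Sample size section.** "assuming type one error of α = 0.05"; power 0.80 (printed there as a value of β); correlation between repeated measures 0.6; group ratio 1:4; effects 0.31 and 0.34; stated totals 205, 170 and 213; attrition 20%; target 265.

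**Reproducing the plan's figures.** Two-sided α and a variance factor of (1 − ρ) = 0.4 are not stated. They are inferred because they return the stated totals exactly.

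- Smaller group: n₁ = (1.96 + 0.842)² × (1 + 1/4) × 0.4 / d².
- d = 0.31: n₁ = 3.925 / 0.0961 = 40.8, so 41 + 164 = 205, as stated.
- d = 0.34: n₁ = 3.925 / 0.1156 = 33.9, so 34 + 136 = 170, as stated.
- Without the factor, d = 0.31 would need 515.
- Attrition: 213 / 0.80 = 266.25, so 267 against the stated 265, which is close.

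**Smallest significant difference at 213 evaluable** (1:4 gives 42.6 and 170.4; 1/42.6 + 1/170.4 = 0.02934).

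- Repeated-measures inputs: SE = √(0.4 × 0.02934) = 0.108; 1.96 × SE = 0.212 SD. The non-significant band runs from −0.212 to +0.212, a width of 0.425 SD.
- Contrast at one time point (no gain from repeated measures): SE = √0.02934 = 0.171; 1.96 × SE = 0.336 SD.

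Both analyses are given the same SE here. If weighting carried a design effect of 1.25 to 1.5 (an assumption), the weighted threshold on the repeated-measures inputs would rise from 0.212 to 0.237–0.260 SD, which widens the band.

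**Which changes trigger the rule?**

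| Unweighted → weighted (SD) | p values, SE 0.108 | p values, SE 0.171 |
|---|---|---|
| 0.10 → 0.20 (doubled) | 0.36, 0.065: not triggered | 0.56, 0.24: not triggered |
| +0.155 → −0.155 (sign reversed) | 0.15, 0.15: not triggered | 0.37, 0.37: not triggered |
| 0.62 → 0.31 (halved) | <0.001, 0.004: not triggered | <0.001, 0.07: triggered |
| 0 → 0.31 | 1.0, 0.004: triggered | 1.0, 0.07: not triggered |

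At the larger SE, a halving escapes the rule only if it starts above 2 × 0.336 = 0.67 SD.

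**How large a shift is plausible?** If a fraction q of a group is lost and the lost differ from those seen by δ, the group mean moves by q × δ. The article gives no δ.

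- Assumed δ = 0.5 SD, q = 0.20: shift = 0.10 SD; 0.10 / 0.31 = 0.32, about a third of the planning effect.
- For a shift of 0.31 SD at q = 0.20: δ = 0.31 / 0.20 = 1.55 SD in one group, or 0.155 / 0.20 = 0.775 SD in opposite directions in both.
- At q = 0.40, the corresponding figures are about 0.78 and 0.39 SD.

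**The case against.** **The text says if, not only if.** Read literally, the sentence sets a duty for discordant tests and is silent on concordant ones. It does not say that the weighted result will be withheld, or which analysis would stand alone. That is right, and a reader who infers an outright ban on showing both goes beyond the text. Still, a promise tied to a condition has a purpose only if reporting may differ when the condition fails, and nothing else in the article fills the gap.

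**This is detail for the analysis plan.** Tabulation of sensitivity analyses is commonly settled there, and that document is not shown. But the article does not merely leave the matter open: it fixes a trigger, and the trigger is a poor one. If the full plan already promises both sets of estimates, only the article's sentence needs aligning.

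**The effect on results could be overstated.** A reader might infer that a shift as large as the planned effect can routinely disappear, for example a published estimate near zero with an adjusted one near 0.31. The documents do not support that. On the inputs that reproduce the plan's sample sizes, 0 to 0.31 changes the test and both results would be reported. It escapes only for a contrast at one time point. At 20% attrition it would also need those lost to differ by about 1.55 SD in one group. This part of the objection stands and limits the point to smaller shifts.

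**Conclusion.** The point holds as a minor one about result-dependent reporting. The only commitment to show both analyses rests on differing test verdicts, and at the planned size those verdicts are insensitive to shifts worth knowing about. The realistic magnitude is about 0.10 SD, a third of the planning effect. A shift of that size changes the verdict only when the two estimates straddle the threshold of about 0.21 SD (repeated measures) or 0.34 SD (one time point).

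This rests on several assumptions:

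- two-sided testing and the (1 − ρ) factor, both inferred from the stated totals;
- a 0.5 SD difference between lost and seen patients, which is illustrative;
- the NPSI effect of 0.31 as a yardstick for pain modulation and immune markers, for which the article gives no effect size;
- a comparator of 170. The no-pain group will be smaller, because fracture patients with other pain states are set apart, and the thresholds would then be wider.

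The calculation shows what the rule permits. It does not show that any result will be left out.

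**What to change.** Replace the reporting sentence in the Missing data section with: *Whenever the inverse-probability-weighted (or other attrition sensitivity) analysis is run, its estimates and 95% confidence intervals will be reported beside the unweighted ones, whether or not the hypothesis tests differ.*

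This leaves the decision to run the weighting as the article has it and does not require weighting for every contrast. The cost is one sentence and extra columns in the results tables, or a supplement for high-dimensional markers such as the RNA sequencing data. Sample size and data collection are unaffected. The article says that no analysis has yet been carried out, so the change can still be made before any results are known.
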